### 2.7 Participant trajectories

Regardless of group allocation, all participants will continue to follow their usual care and minimize the use of other interventions (e.g., pain medications, physical therapy) during the study period. All medication will be monitored throughout the trial.

### 2.8 Outcomes

#### 2.8.1 Primary outcomes.

Mean pain during walking for the most painful foot during the past week: visual analog scale (from 0 to 10, 0 being no pain and 10 pain as bad as it could be).

#### 2.8.2 Secondary outcomes.

Foot Function Index (FFI): The FFI is a widely used, valid, and reliable self-administered questionnaire consisting of 23 items grouped into 3 domains: foot pain (9 items), disability (9 items), and activity limitation (5 items) [31].Global rating of change (GROC): participants’ perception of overall treatment effect will be measured using the self-reported global rating of change scale [32]. This outcome will then be dichotomized into the categories of “effective” (“a very great deal better”, “a great deal better”, “a good deal better” and “moderately better”) and “ineffective” (“somewhat better”, “a little better”, “about the same, hardly any better at all”, “no change”, “about the same, hardly any worse at all”, “a little worse”, “somewhat worse”, “moderately worse”, “a good deal worse”, “a great deal worse” and ‘a very great deal worse”) [33].Health-related quality of life (HRQoL): the 5-level EQ-5D (EQ-5D-5L) will be used [34]. The descriptive system comprises five dimensions: mobility, self-care, usual activities, pain/discomfort and anxiety/depression. Each dimension has 5 levels: no problems, slight problems, moderate problems, severe problems and extreme problems. The participant will be asked to indicate his/her health state by ticking the box next to the most appropriate statement in each of the five dimensions. This decision results in a 1-digit number that expresses the level selected for that dimension. The digits for the five dimensions can be combined into a 5-digit number that describes the patient’s health state.

#### 2.8.3 Other variables.

Gender: Male, female or other.Age: in years (from the date of birth).Weight: in kg (measured in clinic).Height: in meters (measured in clinic).Body Mass Index (BMI): will be calculated with the formula weight (Kg) divided by height squared (meters^2^).Foot Posture Index (FPI): The six clinical criteria used in FPI are: 1. Palpation of the talus head (medial and lateral deviation of the talus head in relation to the navicular bone); 2. Curvature of the supra and lateral inframaleolar region; 3. Position of the calcaneus in the frontal plane; 4. Prominence of the talonavicular region; 5. Congruence of the internal longitudinal arche; and 6. Abduction/adduction of the forefoot with respect to the rearfoot. Each criterion is rated between −2 and +2 and the sum of all gives a total score indicating the foot posture (Normal = 0 to +5; pronated = +6 to +9; highly pronated = +10 to +12; supinated = −1 to −4 and highly supinated = −5 to −12).Effects of the FOs on plantar pressure: peak plantar pressure during a stance phase (kPa) under the metatarsal heads, measured with a Pedar-X in-shoe pressure measurement system (Novel Corporation, Munich, Germany). This system is repeatable and can be used as a valuable tool in the assessment of in-shoe plantar pressure distribution [35–37].

### 2.9 Sample size

To calculate pooled variance (σp²) and square of detectable difference (Δ²), we relied on pain data from a 3-month clinical trial with customized foot orthoses [6] and sham FOs [38].

**Pooled standard deviation:** σ_p_ ≈ 2.71 → σ_p_² ≈ 7.34**Detectable difference:** Δ = 1.49 → Δ² ≈ 2.22**Justification of Δ:** δ = 1.49 corresponds to the minimum clinically important difference on the VAS (≈15% of the scale), based on the study by Reina-Bueno, Vázquez-Bautista [38].α = 0.05β = 0.2**Sum of critical values squared:** (Z_1−α/2_ + Z_1−β_)² = (1.96 + 0.84)² ≈ 7.84

Considering the longitudinal design with three repeated measurements per participant (baseline, 6 weeks and 12 weeks), we estimated the effective variance per subject using a linear mixed-effects model with random intercept:

$${var}_{subj}=\;\sigma_{b}^{\text{2}}+\frac{\sigma_{w}^{\text{2}}}{m}\approx \text{1}.\text{4}\text{6}\text{8}+\;\frac{\text{5}.\text{8}\text{7}\text{2}}{\text{3}}\approx \text{3}.\text{4}\text{2}\text{5}$$

Using this variance, the sample size formula for two independent groups:

$$n\approx \frac{\text{2}\times ({\text{Z}}_{\text{1}-\alpha /\text{2}\;}+\;{\text{Z}}_{\text{1}-\beta })²\;\times {var}_{subj}}{\Delta^{\text{2}}}\approx \text{2}\text{5}$$

Therefore, the minimal sample size would be 25 per group. Considering an attrition rate of 20%, the final sample size should be 32 participants per group, resulting in a total sample size of 64 participants to detect significant differences for the primary outcome (VAS pain) at the primary timepoint (12 weeks). A sensitive analysis table showing required sample sizes under the different correlations (ρ = 0.3, 0.5, 0.7) is available in Supplementary Table S3 in S1 File.

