### 2.10 Statistical analyses

All analyses will follow the intention-to-treat principle, with additional per-protocol sensitivity analyses. Baseline characteristics will be summarized using means for continuous variables and frequencies (%) for categorical variables, without statistical testing between groups.

For the primary outcome (VAS pain), between-group differences will be analyzed using linear mixed-effects models, with participants included as random effects and baseline scores and minimization factors included as fixed covariates. The primary analysis will focus on the change from baseline to week 12, adjusted for baseline values, to provide a more precise estimate of the treatment effect. This approach allows all available baseline and follow-up data to be used, even in the presence of missing outcomes, under the assumption that data are missing at random. If the assumption of normally distributed residuals is violated, generalized linear mixed models will be considered as an alternative.

Secondary continuous outcomes (FFI – foot pain, FFI – disability, FFI – activity limitation, EQ-5D-5L index) will be analyzed using the same approach. The Global Rating of Change (GROC) will be modelled using ordinal logistic regression; a dichotomized responder analysis (effective vs ineffective) will be presented as exploratory. No formal multiplicity adjustments will be applied, but results will be interpreted with caution.

If missing data exceed 10% for the primary outcome, multiple imputation by chained equations will be used as a sensitivity approach, including all variables related to missingness and outcome prediction in the imputation model. Sensitivity analyses will also be performed under non-Missing At Random assumptions (e.g., using delta-adjustment or pattern-mixture models) to assess the robustness of the findings to departures from the Missing At Random assumption.

Concomitant care and rescue medication use will be recorded descriptively throughout the trial and summarized by treatment group. If substantial between-group differences are observed, these variables will be considered in sensitivity analyses.

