The plantar pressure will be divided in nine-foot regions [39]. The analyses will be analyzed with Statistical Parametric Mapping (SPM1D, www.spm1d.org). We will assess the normality of the distribution of the peak plantar pressure (spm1d.stats.normality.anova1rm function) and followed by SPM paired t-tests SPM(t) as post hoc analyses will be used to compare the peak plantar pressure across with and without FOs, when the data will be normally distributed. The non-parametric version, SnPM(t) tests, will be use when data will not normally distributed.

All this will be carried out in frequency distribution tables of different categories, using SPSS (IBM SPSS Statistics: V.28, USA) and plantar pressure will be implemented in MATLAB R2024b (The MathWorks Inc., Boston, MA, USA) using open access scripts (www.spm1d.org).

No additional analyses (e.g., subgroup and adjusted analyses) are planned for this study. The two-sided level of p will be set at 0.050.

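### The sample size uses the variance of a three-visit mean that includes baseline, but the primary contrast is at week 12: power is about 51%, not 80%, at the plan's implied correlation

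*Protocol article*

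**What the plan says.** Section 2.9 of the protocol article takes a single-score variance from earlier pain data ("σ_p_ ≈ 2.71 → σ_p_² ≈ 7.34") and a target difference on the 0–10 scale ("Δ = 1.49 → Δ² ≈ 2.22"). It then reduces the variance: "Considering the longitudinal design with three repeated measurements per participant (baseline, 6 weeks and 12 weeks), we estimated the effective variance per subject". The formula is the between-person variance plus one third of the within-person variance, 1.468 + 5.872/3 ≈ 3.425. Put into the two-group formula, this gives 25 per group, raised to 32 per group (64 in total) for 20% attrition.

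The same section says this number serves "to detect significant differences for the primary outcome (VAS pain) at the primary timepoint (12 weeks"). It refers to a supplementary table of "required sample sizes under the different correlations (ρ = 0.3, 0.5, 0.7").

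Section 2.10 defines the test: "The primary analysis will focus on the change from baseline to week 12, adjusted for baseline values". The model is a linear mixed model with a participant random effect, and baseline score and the minimization factors are fixed covariates.

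**The concern.** The variance in the sample-size formula has to be that of the quantity being tested. Dividing the within-person variance by 3 is right only if the test compares each participant's mean over three visits, all carrying the full treatment effect. Neither condition holds. The declared contrast is at week 12 alone. Baseline is measured before treatment, so it carries no treatment effect, and section 2.10 already uses it as a covariate.

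The formula also responds to the correlation ρ between visits in the wrong direction. In it, a higher ρ raises the required n. For a baseline-adjusted contrast, a higher ρ makes baseline more informative and lowers the required n.

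If the real power is well below 80%, a true effect at the plan's own minimum important difference could easily be missed. A null result might then be read as evidence against the orthoses when the trial was too small to tell.

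**Working it through.** **Inputs** (section 2.9 unless noted)

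- α and β: "α = 0.05β = 0.2"; two-sided according to section 2.10 ("The two-sided level of p will be set at 0.050"). Squared sum of critical values: (1.96 + 0.84)² = 7.84.
- Δ = 1.49, Δ² = 2.22; total variance σ² = 7.34.
- Variance components 1.468 (between) and 5.872 (within). They sum to 7.34, so the implied ρ = 1.468/7.34 = 0.20. The article does not state this value in words.
- Attrition 20%; allocation 1:1 (section 2.4).

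**Step 1. The plan's figure reproduces.** 1.468 + 5.872/3 = 3.425. Then n = 2 × 7.84 × 3.425 / 2.22 = 24.2, rounded up to 25, and 25/0.8 = 31.25, rounded up to 32. Power at 25 per group with this variance is 81%. The arithmetic is sound; the variance is the problem.

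**Step 2. Variance of the declared contrast.** Under a random-intercept model any two visits have correlation ρ. Regressing the week-12 score on baseline leaves variance σ²(1 − ρ²). Using the change score instead gives the same result once baseline is a covariate, because only the baseline coefficient shifts. At ρ = 0.20: 7.34 × (1 − 0.04) = 7.046.

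**Step 3. Sample size and power at ρ = 0.20.**

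- n = 2 × 7.84 × 7.046 / 2.2201 = 49.8, so 50 per group; 50/0.8 = 62.5, so 63 enrolled per group.
- Power at 25 per group = Φ(1.49/√(2 × 7.046/25) − 1.96) = Φ(1.985 − 1.96) = 51% (49% with the noncentral t).
- Difference detectable with 80% power = 2.8 × √(2 × 7.046/25) = 2.10 points.

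**Step 4. The same over the plan's own correlations**, with σ² = 7.34:

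| ρ | Variance σ²(1 − ρ²) | Power, 25 per group | Detectable difference | Evaluable (enrolled) per group for 80% | Plan's formula: evaluable (enrolled) per group |
|---|---|---|---|---|---|
| 0.2 | 7.05 | 51% | 2.10 | 50 (63) | 25 (32) |
| 0.3 | 6.68 | 53% | 2.05 | 48 (60) | 28 (35) |
| 0.5 | 5.51 | 61% | 1.86 | 39 (49) | 35 (44) |
| 0.7 | 3.74 | 78% | 1.53 | 27 (34) | 42 (53) |

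The last column applies the printed formula, with variance σ²[ρ + (1 − ρ)/3], to each ρ. It shows two things. The base case of 0.20 lies outside the plan's list, and every value in the list would require more than 32 per group even by the plan's own formula. The last two columns also move in opposite directions as ρ rises.

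**Step 5. Averaging in baseline would not help.** Suppose the three-visit mean were tested and the effect were a constant 1.49 at weeks 6 and 12. The expected difference would be 2/3 × 1.49 = 0.99, and power at 25 per group would be Φ(0.993/√(2 × 3.425/25) − 1.96) = 48%. The formula takes the smaller variance but keeps the full 1.49.

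**The case against.** Five points can be made for the plan.

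- **The 51% is conditional.** It rests on an inferred ρ of 0.20 and sits at the low end of a 51% to 78% range. At ρ of about 0.73, 25 per group would give about 81%. This stands, so the range belongs beside the headline. But 0.20 is what the plan's own components imply, and no correlation in its list reaches 80%.
- **25 per group assumes the full planned attrition.** If all 32 are evaluable, power is 61% at ρ = 0.2, 72% at 0.5 and 87% at 0.7. This also stands, but the claim of 80% was made for 25, after attrition.
- **The mixed model uses week 6.** With complete data and a week-12-specific effect, week 6 adds nothing under a random intercept once baseline is a covariate. With dropout it recovers a little. In a best case at ρ = 0.7, where 20% miss week 12 but everyone has week 6, power is about 80%. At ρ = 0.2 the gain is negligible.
- **Section 2.10 names no group-by-time term.** If one common effect over weeks 6 and 12 were estimated, the variance at ρ = 0.2 would be 4.11. Power would then be 74% with 25 per group, and 30 evaluable (38 enrolled) would be needed. Both sections point to week 12, however, and this reading also falls short of 80% at the implied ρ. Adjusting for age and gender might lower the variance further, but the article gives no figure.
- **The supplementary table is not shown.** Whether it uses the same formula, or gives a source for ρ, cannot be checked. The grid figures above come from the printed formula, and the lack of a source can be asserted only of the article text.

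**Conclusion.** The concern holds. The calculation is internally correct, but its variance belongs to a quantity the trial will not test. At the plan's implied ρ and after planned attrition, the stated 80% overstates power by about 29 percentage points, and the evaluable number needed is twice the one given (50 against 25 per group). The shortfall narrows as ρ rises and is small at 0.7, so its size depends on a value the article does not justify. These figures assume total variance 7.34 at each visit, equal correlation between visits, a normal approximation, and no gain from the other covariates. The sole justification for 64 participants is wrong as written and must be corrected.

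**What to change.** In section 2.9:

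1. Replace the three-visit-mean variance with that of the declared contrast, σ²(1 − ρ²).
2. State the ρ used and its source.
3. Check the supplementary table. If it uses the printed formula, rebuild it with the corrected one, and include ρ = 0.2.
4. Replace the power claim with wording such as:

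> With 25 evaluable participants per group, a two-sided 5% test of the baseline-adjusted week-12 difference has about 51% power for 1.49 points if the correlation between visits is 0.2, and 78% if it is 0.7. The difference detectable with 80% power is 2.1 and 1.5 points respectively.

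This costs wording and one table and needs no extra participants, but the stated power becomes less favourable. It corrects the claim without curing the low power. If the sponsor wants 80% for 1.49 points at week 12, the cost is 63 enrolled per group (126 in total) at ρ = 0.2, or 34 per group at ρ = 0.7. If a common effect over weeks 6 and 12 is what is intended, section 2.10 must declare it as the primary contrast and section 2.9 must be sized for it (38 enrolled per group at ρ = 0.2). Any such choice should be made without sight of outcome data by group.

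### The sample size rests on an unstated within-person correlation of 0.2, below every value in the plan's own sensitivity set, and 25 per group does not give 80% power at any of the listed values

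*Protocol article*

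**What the plan says.** Section 2.9 (Sample size) takes one pooled standard deviation and variance from published pain data, "σ_p_ ≈ 2.71 → σ_p_² ≈ 7.34", and a target difference, "Δ = 1.49 → Δ² ≈ 2.22". The error rates are "α = 0.05β = 0.2", and section 2.10 confirms that the test is two-sided: "The two-sided level of p will be set at 0.050".

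For the three visits the section then says that "we estimated the effective variance per subject using a linear mixed-effects model with random intercept". It enters 1.468 for the between-person component and 5.872/3 for the within-person part, which gives 3.425. The conclusion is: "Therefore, the minimal sample size would be 25 per group". A 20% attrition allowance raises this to 32 per group, 64 in total, for VAS pain at 12 weeks.

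The paragraph ends by pointing to a supplement: "A sensitive analysis table showing required sample sizes under the different correlations (ρ = 0.3, 0.5, 0.7"). The article text gives no correlation, dataset or source for the two components.

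Section 2.10 sets the primary analysis as the change from baseline to week 12, adjusted for baseline, in a linear mixed model.

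**The concern.** Variance components fitted to repeated measurements would not be expected to fall on an exact 20/80 split of a variance taken from elsewhere. The figures look like an assumption described as an estimate. The assumption decides the result: in the printed formula the required number rises with the correlation, and the value used is smaller than all three values offered as sensitivity cases. A sensitivity range would normally bracket its base case, and this one leaves it out.

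At stake is how the result will be read. If the trial finds no difference, readers will treat it as a study with 80% power to detect 1.49 points. That figure depends on an input they cannot see in the article.

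**Working it through.** **Inputs, all from section 2.9:** pooled variance 7.34; Δ = 1.49, Δ² = 2.22; squared sum of critical values 7.84; m = 3 visits including baseline; 20% attrition. The correlations are the three listed values plus the implied one.

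**1. Reproduce the plan's figure.** 1.468 + 5.872/3 = 3.425. Then n = 2 × 7.84 × 3.425 / 2.22 = 24.19, rounded up to 25, and 25/0.8 = 31.25, rounded up to 32. The printed arithmetic is correct.

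**2. Identify the hidden input.** 1.468/7.34 = 0.200; 5.872/7.34 = 0.800; 1.468 + 5.872 = 7.34. Under a random intercept, ρ = σ_b²/(σ_b² + σ_w²) = 0.2.

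**3. Apply the printed formula to the plan's own range.** Variance = 7.34 × [ρ + (1 − ρ)/3]; n = 2 × 7.84 × variance / 2.22; power at 25 per group = Φ(1.49/√(2 × variance/25) − 1.96).

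| ρ | Variance | n per group | After 20% attrition | Power at 25 |
|---|---|---|---|---|
| 0.2 (implied) | 3.425 | 24.19, so 25 | 32 | 81% |
| 0.3 | 3.915 | 27.65, so 28 | 35 | 76% |
| 0.5 | 4.893 | 34.56, so 35 | 44 | 66% |
| 0.7 | 5.872 | 41.47, so 42 | 53 | 58% |

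**4. Repeat for the comparison named in section 2.10.** The formula in step 3 averages baseline with the follow-up visits, whereas the target is week 12 adjusted for baseline. If 7.34 is the variance of a score at one visit, the adjusted variance is 7.34 × (1 − ρ²). The power formula is the same. The detectable difference at 25 per group is 2.8 × √(2 × variance/25).

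| ρ | Variance | n per group for 80% | Power at 25 | Detectable difference at 25 | Power at 32 |
|---|---|---|---|---|---|
| 0.2 | 7.046 | 50 | 51% | 2.10 | 61% |
| 0.3 | 6.679 | 48 | 53% | 2.05 | 64% |
| 0.5 | 5.505 | 39 | 61% | 1.86 | 72% |
| 0.7 | 3.743 | 27 | 78% | 1.53 | 87% |

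The two tables run in opposite directions. With the printed formula, power at 25 per group falls as ρ rises; for the week-12 comparison it rises. Both stay below 80% at 0.3, 0.5 and 0.7. All of these are normal approximations; a noncentral t calculation lowers the power at 25 per group by about 1 to 2 percentage points.

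**The case against.** The strongest reply is that nothing is miscalculated and that the article does disclose dependence on the correlation. This is partly right.

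- **The arithmetic is sound.** The 25 and the 32 both reproduce. The fault is an undisclosed assumption described as an estimate.
- **The supplement is not available here.** Supplementary Table S3 may state or justify 0.2. The point therefore concerns the article text only. Even so, if the table applies the printed formula to the listed values, each row exceeds 25.
- **A reader might infer that the plan claims 25 per group holds across the listed correlations.** It does not. It says only that a table shows the sizes required at each value.
- **A reader might infer that 76%, 66% and 58% are the trial's real power, or that 0.2 is the most favourable choice in general.** Neither is supported. Those figures come from a formula that averages baseline with follow-up. For the week-12 comparison, 0.2 is the least favourable of the four values.
- **Twenty-five is the number left after the full 20% loss.** With all 32 analysed, the printed formula gives 85% at ρ = 0.3 but 77% and 69% at 0.5 and 0.7. The week-12 comparison reaches 87% at ρ = 0.7 only. At ρ = 0.5 both fall short even with no loss.
- **Another analysis could do better.** Baseline-adjusted analysis of the mean of both follow-ups gives 90% at ρ = 0.7 with 25 per group. That is neither the printed formula nor the stated week-12 target, and it still gives 74% and 79% at 0.3 and 0.5.

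**Conclusion.** The concern holds in this form: the 25 per group depends on a within-person correlation of 0.2 that the article text does not state and that lies outside its own sensitivity set. At each listed correlation, 25 per group misses 80% power, both by the printed formula (about 76%, 66%, 58%) and for the baseline-adjusted week-12 comparison (about 53%, 61%, 78%). The first set shows only that the formula and the range contradict each other. The second set is the one that bears on the planned analysis.

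Three assumptions carry this. The listed ρ is read as the within-person correlation, which is the natural reading next to a random-intercept formula but is an inference. For the week-12 figures, 7.34 is taken as the variance of a single-visit score; section 2.9 does not say whether it comes from baseline, endpoint or change scores. The headline figures are for 25 analysed per group, as the plan's attrition allowance implies.

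A reader might go further and conclude that the trial must recruit more participants. That does not follow: what needs correcting is the stated power, and this can be done with 64 participants fixed.

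**What to change.** Keep 64 participants and revise section 2.9 and its supplementary table as follows.

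1. Say that the components are an assumed split of 7.34, and give ρ = 0.2 with its basis.
2. Make the base case and the sensitivity range consistent, so that the range includes the planning value.
3. State which kind of score the variance 7.34 describes.
4. Replace the 80% claim with power or detectable difference across ρ = 0.2 to 0.7, computed for the baseline-adjusted week-12 comparison of section 2.10. If 7.34 is a single-visit variance, the values at ρ = 0.2, 0.3, 0.5 and 0.7 are those in the second table: with 25 per group, power of about 51%, 53%, 61% and 78%, or detectable differences of about 2.10, 2.05, 1.86 and 1.53 points; with all 32 per group, power of about 61%, 64%, 72% and 87%.
5. Do not print 76%, 66% and 58% as the trial's power.

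The cost is one rewritten paragraph and one revised table, with no change to recruitment, conduct or analysis. The downside is a less favourable power statement.
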